A frequently used approach for identifying factors associated with help-seeking is Andersen’s behavioural model of health services use behaviour.^48^ The model hypothesises a number of factors to be associated with help-seeking behaviour: (1) predisposing factors including sociodemographic variables (eg, age and gender), and health-related beliefs and knowledge^49^; (2) enabling factors relating to logistical elements to receiving care and resources (eg, financial factors and social support)^50^; (3) external environmental factors (eg, location); and (4) need-related factors (eg, symptoms of psychological distress). Recently, the model has been adopted to examine factors associated with accessing both traditional and e-MH services within a young adult (aged 18–39 years) population.^32^ Interestingly, the study identified a weaker utilisation of e-MH by young people who had experienced negative childhood experiences during childhood (eg, family conflict, bullying or lack of affection).^32^ This finding is of particular importance seeing that negative experiences of childhood are normally associated with increased mental healthcare utilisation.^51^ Furthermore, given evidence to suggest some AYACCS may experience bullying related to their cancer experience^52^ and poor family functioning for example conflict,^53^ it may be important to examine whether negative childhood experiences are associated with reduced mental healthcare utilisation in an AYACCS population. Furthermore, to the best of our knowledge, Andersen’s behavioural model of health services use has not yet been applied to an AYACCS population and factors associated with help-seeking in the population remain unclear.

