#### Sample size estimation

The Swedish Childhood Cancer Registry has some 9880 Swedish persons diagnosed when 0–18 years registered since 1982. However, some will have been classified as having a benign tumour, some have been registered twice and some will be deceased. As such, the number of potentially eligible cases will be lower and estimated to be approximately 5745. Sample size calculation indicated that a minimum of 365 participants would be required, with a power of 0.9 and p<0.05 (two-tailed). Assuming a response rate of approximately 40%, as indicated by a systematic review of participation rates in self-administered questionnaire studies with childhood cancer survivors,^69^ we estimate inviting 913 potential participants to achieve the required sample size.

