### Survey items

An online and paper-based survey, consisting of 98 items in Swedish. The survey comprises eight subsections: (1) sociodemographic characteristics (11 items); (2) clinical cancer-related characteristics (3 items); (3) actual help-seeking behaviour (2 items); (4) attitudes towards internet-administered interventions (17 items); (5) stigma of mental illness (5 items); (6) MHL (26 items); (7) social support (12 items); and (8) current symptoms of depression, anxiety and stress (21 items). One open question at the end of the survey offers and opportunity to provide any further information concerning emotional distress and preferences for support after childhood cancer. Potential predisposing, enabling, environmental, and need-related factors examined with the survey are summarised in table 1.

**Table 1 T1:** Factors to be examined as per Andersen’s behavioural model of health services use

Andersen’s behavioural model of health services use	Factors*
Predisposing	Sex (male/female/other) Age (16–24/25–39) Time since first cancer treatment (years) Place of birth (born in Sweden/born outside of Sweden) Childhood negative events (yes/no) Level of education (≤upper secondary school/>upper secondary school) Public stigma (Stigma Scale for Receiving Psychological Help) Mental health literacy
Enabling	Type of cancer (leukaemia/central nervous system tumour/solid tumour/lymphoma/other) Relationship status Employment status (yes/no/studying) Social support (12-item Interpersonal Support Evaluation List)
Need-related	Symptoms of depression (DASS-21 depression subscale) Symptoms of anxiety (DASS-21 anxiety subscale) Symptoms of stress (DASS-21 stress subscale) Self-reported experience of mental health difficulties in past 6 months (yes/no)
Environmental	Region of Sweden (south/mid/north) Rural or urban area
Actual help-seeking behaviour (dependent variable)	Receipt of mental health support in the past 6 months Type of mental health support received in the past 6 months (formal/technology/informal)

*Outcomes selected informed by previous research.^32 42 50 70^

DASS-21, Depression Anxiety and Stress Scale.

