
### Data analysis

#### Statistical analysis

All statistical analyses will be conducted using SPSS V.26.0 software (IBM SPSS Statistics for Windows, 2019, Armonk, New York, USA). Sociodemographic and clinical characteristics will be presented with descriptive statistics. The potential association between predicting factors as informed by Andersen’s behavioural model of health services use (predisposing, enabling, environmental, and need-related factors) and the dependent variable help-seeking behaviour, for example, receipt of mental health support in the past 6 months will be examined using univariable and multivariable logistic regressions.^70^ The non-help-seeking group will used as the reference group.^70^ First, univariable analyses will be conducted for each predictor separately. Variance inflation factor will be used to examine multicollinearity prior to the regression analysis. A multivariable logistic regression will be performed using stepwise manual backward selection procedure. All predictor variables will initially be included, and non-significant predictors will be eliminated with only variables significantly related to the dependent variable (p<0.05) retained. For both the univariable and multivariable logistic regressions, ORs will be presented, alongside 95% CIs, and p values. Given the heterogeneous nature of the study population, subgroup analysis will be performed by stratifying the population by age and sex. The same method of modelling will be used for the subgroup analyses for age (15–19 years vs 20–29 years vs 30–39 years) and sex (male vs female). The subgroup analysis will be exploratory and with results used to inform subsequent studies.

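### The one multivariable model conditions predisposing factors on current need and then deletes by p value, so there is no multivariable estimate free of need and a factor acting through need would usually drop out

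*Protocol article*

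**What the plan says.** The Statistical analysis section sets out two stages. The first is crude: "First, univariable analyses will be conducted for each predictor separately". The second reads "A multivariable logistic regression will be performed using stepwise manual backward selection procedure". Its starting set and deletion rule are fixed: "All predictor variables will initially be included, and non-significant predictors will be eliminated", "with only variables significantly related to the dependent variable (p<0.05) retained". No blocks or order of entry are given. ORs, 95% CIs and p values are promised for both stages. The same modelling is repeated in exploratory subgroups by sex and by three age bands.

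Table 1 (Survey items) supplies the factors. "Childhood negative events (yes/no") is listed as predisposing. The need-related group holds the three DASS-21 subscales and self-reported mental health difficulties in the past 6 months. All of these therefore start in the same model.

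The Help-seeking behaviour section of the Introduction singles out one predisposing factor. It says it may be important to "examine whether negative childhood experiences are associated with reduced mental healthcare utilisation in an AYACCS population", and notes that such experiences usually go with more use of care. Research question 1 asks about associations and does not say whether they are overall or at a given level of need.

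**The concern.** Childhood events come before the symptoms measured in the survey, and help-seeking is defined as having sought and received professional support for mental health difficulties in the past 6 months. Difficulties are thus close to a precondition of the outcome. If childhood events raise later need, and need leads to help-seeking, a model holding need fixed removes that part of the association. The p<0.05 rule then removes the factor.

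The reader would be left with a crude OR, unadjusted for anything, and a need-conditional OR that appears in the final model only if it reaches significance. An OR adjusted for background factors but not for need appears nowhere in the main analysis, although it is the natural figure to set beside the usual direction of association named in the Introduction. This matters because the Discussion proposes to use factors negatively associated with help-seeking as intervention targets. A factor can be negative at equal need while those who have it use care as often as others do.

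**Working it through.** **Plan's own figures.** The sample size enters only as n=365: "Sample size calculation indicated that a minimum of 365 participants would be required, with a power of 0.9 and p<0.05 (two-tailed"). The article gives no effect size, outcome rate or test, so 365 can be neither reproduced nor refuted, and this point does not dispute it. The invitation count reproduces: 365/0.40 = 912.5, rounded up to 913.

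**Model for the check.** Let x be the binary predisposing factor, L = δx + ε the latent need (ε standard normal), and logit P(help-seeking) = a + βL + γx.

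- Given need, the log-OR of x is γ.
- Without conditioning on need it is roughly γ + βδ, shrunk somewhat by averaging over ε.

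With γ = 0, δ = 0.5 and β = 1.2, exp(0.6) = 1.82 before shrinkage; the simulated total OR is 1.60. With γ = log 0.6 = −0.51, δ = 0.5 and β = 1.0, the sum is −0.01, an OR of about 0.99, as simulated.

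**Assumed inputs (none is in the protocol).** 35% exposed; help-seeking 20–30%; δ 0.3–0.8 SD; β 0.8–1.2 per SD of need. Need is observed through three correlated symptom scores and one binary item, and there are 10 noise predictors. Backward elimination runs at p<0.05, with 600 runs per scenario. The Monte Carlo standard error is at most √(0.5×0.5/600) = 0.02.

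| Direct OR | δ | β | Help-seeking | Total OR | Univariable p<0.05 | Pre-need model p<0.05 | Kept by backward elimination | Univariable p<0.05 but dropped |
|---|---|---|---|---|---|---|---|---|
| 1.0 | 0.3 | 0.8 | 20% | 1.25 | 13% | 14% | 6% | 9% |
| 1.0 | 0.5 | 1.2 | 30% | 1.60 | 53% | 53% | 4% | 49% |
| 1.0 | 0.8 | 0.8 | 30% | 1.75 | 66% | 67% | 9% | 58% |
| 1.0 | 0.8 | 1.2 | 20% | 2.19 | 81% | 80% | 7% | 75% |
| 1.0 | 0.8 | 1.2 | 30% | 2.11 | 90% | 90% | 8% | 83% |
| 1.5 | 0.5 | 1.0 | 25% | 2.17 | 87% | 85% | 42% | 45% |
| 0.6 | 0.5 | 1.0 | 25% | 0.99 | 4% | 5% | 37% | 1% |
| 1.0 | 0 | 1.0 | 25% | 1.00 | 6% | 6% | 7% | 2% |

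Over all 12 scenarios with no direct effect (five are shown), backward elimination kept the factor in 4–9% of runs. In the last row, where the factor has no association at all, it kept it in 7%. Retention is therefore at about chance level however large the total association is.

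A separate simulation assumed 40% exposed, δ 0.4–0.8 SD, a need OR of 1.8–2.5 per SD and 20% help-seeking. It gave the same picture: overall OR 1.25–1.90, about 5% significant with need in the model and 14–73% without.

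**Limit of the check.** The noise predictors are unrelated to exposure and outcome, so the close agreement between the univariable and pre-need columns is built in. The check shows what conditioning on need does. It does not measure how far the crude OR would be confounded.

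**The case against.** Four points can be made for the plan.

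1. *The association is not lost.* A reader might infer that the study would report childhood negative events as unrelated to help-seeking. The protocol does not say so. A univariable OR, CI and p value are presented for every predictor, and in the simulations they detect the association about as often as a pre-need model (13–90% against 14–90%). This stands, with the caveat that the simulations contain no confounding. The crude OR remains unadjusted.

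2. *Age and sex are not ignored.* The subgroup analyses repeat the modelling, on a natural reading including the univariable step, within each sex and each age band. This stands too, but these analyses are exploratory, take age and sex one at a time, and adjust for nothing else.

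3. *Adjusting for need suits the question.* A reader might infer that need should be kept out of the model. The documents do not support that, because the Introduction asks about reduced use. In the row with direct OR 0.6, the univariable analysis detects the factor in 4% of runs and the planned model keeps it in 37%. The need-adjusted OR is informative and should stay.

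4. *The path through need is an assumption.* The protocol lists the Andersen domains side by side, draws no causal path, and disclaims cause and effect. DASS-21 measures current symptoms, at the end of the 6-month help window, so it may partly reflect help already received. This stands: mediation is plausible from timing but not stated. It does not rescue the single model, since need scores affected by the outcome would make ORs conditional on them harder to read.

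**Conclusion.** The point holds in a limited form. The main analysis has no multivariable estimate free of current need, does not say that the final ORs apply at equal current need, and gives an adjusted OR for a predisposing factor in the final model only if it survives p<0.05 with need included. A factor acting wholly through need would be kept in about 4–9% of samples of 365. One with a direct OR of 1.5 and a total OR of 2.17 would be kept in 42%.

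The documents do not support the stronger claims that the association disappears from the results, that need adjustment is an error, or that the study would report a reversed association. Whether childhood events act through need in this population is unknown, and every simulation input is assumed. The consequence is an incomplete and unlabelled set of estimates, cheaply repaired and worth repairing before analysis.

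**What to change.** Add a multivariable model without the need factors by entering the Andersen domains in order: predisposing; then enabling and environmental; then need. Report ORs and 95% CIs for the predisposing factors before and after need enters, beside the univariable ORs, and do not delete these factors by p value. Label the full-model ORs 'at equal current need'.

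For childhood negative events, adjust the pre-need estimate for background factors such as age, sex and place of birth. Education, public stigma and mental health literacy also sit in the predisposing domain of Table 1, but they may themselves be later consequences of those events. Adjusting for them would again remove part of the overall association.

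Possible wording: *Associations of predisposing factors with help-seeking will be estimated before and after adjustment for need-related factors. Predisposing factors will be retained regardless of significance. Estimates from the full model describe associations at equal current need.*

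The cost is a few extra regressions and one or two table columns. If the subgroups follow the same scheme, it is repeated in five strata (two sexes, three age bands). It needs no new data and leaves the sample size unchanged.

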## Introduction

Medical improvements have resulted in an overall 5-year survival rate of 81.2% from cancer diagnosed during childhood (0–18 years) in Northern Europe.^1^ However, significant challenges, such as late effects, remain after treatment completion.^2 3^ Survivors of childhood cancer report a number of long-term adverse physical and developmental outcomes^4–6^ and social and economic impacts, including poorer educational and occupational achievements.^7 8^ A further common late effect is symptoms of psychological distress, for example, post-traumatic stress, anxiety and depression, symptoms of which have been found to persist decades postdiagnosis.^9–11^ Difficulties with psychological distress are further complicated given that adolescence is a period of increased vulnerability to mental health problems,^12^ with difficulties such as depression and anxiety commonly first appearing before 24 years of age.^13^ Indeed, individuals diagnosed with cancer during childhood, adolescence and young adulthood have been found to be at an increased likelihood of being prescribed hypnotics and anxiolytics^14 15^ of using antidepressant medication over the long-term,^16^ and are at an elevated risk of suicide.^17^ As such, adolescent and young adult childhood cancer survivors (AYACCS), commonly defined as cancer survivors diagnosed during childhood currently aged between 15 and 39 years,^18^ are particularly vulnerable to experiencing adverse psychological and social outcomes, and there is a significant need for long-term care and support.^5^ However, despite a clear need for the provision of mental health support, a mental health treatment gap remains, with few AYACCS being offered professional psychological support.^19–22^ Reasons for this treatment gap may pertain to a lack of qualified healthcare professionals, poor service provision, geographical barriers^23^ and public stigma (eg, the general public holding negative beliefs about cancer survivors, eg, being less competent).^24^

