### Eligibility criteria

Eligible participants will: (1) be an adolescent or young adult, aged 16–39 years, at study start; (2) have been diagnosed with childhood cancer when 0–18 years; (3) have completed successful cancer treatment (including relapses) at a minimum 3 months ago according to self-report; (4) be able to read and write in Swedish; and (5) currently reside in Sweden.

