#### Swedish Childhood Cancer Registry

Personal identification numbers of AYACCS will be obtained from the Swedish Childhood Cancer Registry (National Quality Registry, initiated in 1982). Next, addresses will be obtained via NAVET, a population registry held by the Swedish Tax Agency. NAVET is continuously updated with important information about the Swedish population, including deaths and can, as such, provide current addresses and information concerning the vital status of AYACCS. The Swedish Tax Agency will provide this information via a secure online file transfer system (e-transport) on the same day information is requested by the study team. Study invitation letters will be sent to AYACCS on the same day that information is provided via e-transport in order to minimise the likelihood of inviting a deceased AYACCS. AYACCS will be invited to participate by the study team on a weekly basis, using blocks of 100 until the target sample size has been reached. Blocks will be selected randomly, with minimisation used to ensure balance between factors that may affect outcomes: sex (male; female); current age (16–24 years; 25–39 years); and age at diagnosis (0–12 years; 13–18 years).

Study invitation packs sent to home addresses will include a study invitation letter, study information, a link to the online survey via the U-CARE portal (www.u-care.se), a secure internet research platform to support data collection and provision of e-MH interventions,^63^ and a study log-in code. All potential participants identified via the Swedish Childhood Cancer Registry and invited via mail-out will be provided with a link to the online survey on the U-CARE portal and a study log-in code. In addition, given evidence to suggest the provision of choice between web-based and paper-based surveys can increase survey response rates among childhood cancer survivors,^64^ we will include a paper-based survey and freepost envelope with each invitation letter.

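### The age-band models must start from every Table 1 factor, but the age factor is constant in two of the three bands, the first band starts below the eligible age, and the youngest band is probably too small for that model

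*Protocol article*

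**What the plan says.** The Statistical analysis section of the protocol article plans exploratory analyses in subgroups defined by sex and by age. On the modelling it states: "The same method of modelling will be used for the subgroup analyses for age (15–19 years vs 20–29 years vs 30–39 years". The method referred to is univariable logistic regression for each predictor, then a multivariable model built by backward elimination: "All predictor variables will initially be included, and non-significant predictors will be eliminated".

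Three other places bear on the age bands:
- Eligibility criteria: a participant must "be an adolescent or young adult, aged 16–39 years, at study start".
- Recruitment, Swedish Childhood Cancer Registry: invitation blocks are balanced on "current age (16–24 years; 25–39 years", among other factors. Table 1 (Survey items) enters age as a predisposing factor with the same two classes.
- Introduction: survivors of this kind are commonly defined as "currently aged between 15 and 39 years". This is a general definition, and a possible source of the lower limit of 15.

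The Discussion supports splitting by age: it expects adolescents to have needs and preferences that differ from those of people in their twenties or thirties.

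**The concern.** Two things follow from the text alone. The first band includes an age that nobody in the study can have at entry. And the instruction to begin from all predictors cannot be carried out in two of the three bands, because everyone aged 16–19 is in Table 1's lower age class and everyone aged 30–39 is in its upper class.

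A third point depends on assumptions. The youngest band spans only 4 of the 24 eligible years of age, so it may hold too few respondents, and too few help-seekers, for a model that starts from all of Table 1. The subgroup results are meant to inform later studies, and adolescents are the group that the Discussion singles out. Elimination at p<0.05 from a starting model with about one event per coefficient or fewer could pass on arbitrary odds ratios for that group.

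**Working it through.** **The plan's own figure.** The sample size section states "a minimum of 365 participants would be required, with a power of 0.9 and p<0.05 (two-tailed" and "Assuming a response rate of approximately 40" per cent. 365 / 0.40 = 912.5, rounded up to 913, which agrees with "we estimate inviting 913 potential participants to achieve the required sample size". The 365 is taken as given.

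**Number of coefficients.** Table 1 lists 8 predisposing, 4 enabling, 4 need-related and 2 environmental factors, 18 in all. With categories dummy-coded, relationship status taken as binary and mental health literacy as one score, the groups contribute 9 + 8 + 4 + 3 = 24 coefficients. Removing the constant age factor leaves 23. Removing the rare third sex class as well leaves 22.

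**Size of the 16–19 band** (assumptions; the article gives no age distribution):
- Ages even over 16–39: 365 × 4/24 = 60.8, and 365 × 10/24 = 152 in each of the other bands.
- Half of respondents aged 16–24 and half 25–39, even within each: 182.5 × 4/9 = 81.1. The 20–29 band is then 182.5 × 5/9 + 182.5 × 5/15 = 162, and the 30–39 band 182.5 × 10/15 = 122.

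**Events at an assumed 10/20/30% help-seeking.** n=61: 6/12/18. n=81: 8/16/24. Per coefficient this runs from 6.1/22 = 0.28 to 24.3/22 = 1.10.

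**Can the starting model be fitted?** The maximum likelihood estimate is not finite if some non-zero b gives (2yᵢ − 1)xᵢ′b ≥ 0 for every respondent and > 0 for at least one (complete or quasi-complete separation). This was checked by linear programming on simulated data with 22 coefficients. Category shares were assumed (for example, cancer type 32/25/20/13/10%) and a latent distress factor drove help-seeking. Percentage of samples without a finite estimate:

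| Band size | 10% | 20% | 30% |
|---|---|---|---|
| 61 | 99 | 82 | 52–55 |
| 81 | 94–95 | 48–51 | 17–20 |
| 122 | 69 | 14 | 3 |
| 152 | 51–58 | 10–16 | 1–2 |
| 365 (whole sample) | 3 | 1 | 0 |

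A range shows two separate sets of runs. With 200 runs the Monte Carlo standard error is at most √(0.25/200) = 3.5 percentage points.

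**Sparse classes kept.** With an assumed 2% in the third sex class and 5% above upper secondary school (23 coefficients), the figures are 100/96–97/87–89% at n=61 and 99/85–90/73–75% at n=81.

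**Which remedy works?** With 6 parameters in the existing youngest band, separation falls to 18–28/1–4/0% at n=61 and 6–12/1/0% at n=81, depending on the assumed mix. Changing only the bands to 16–24/25–39 and keeping 22 coefficients leaves 60/12/1% in the younger band if ages are even (365 × 9/24 = 137), or 35/3/0% if selection is balanced (n=183).

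**The case against.** The strongest reply has four parts.

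*The label is trivial.* No 15-year-old can enrol, so no estimate changes, and a constant covariate simply drops out on stratifying. Both are true. They remain errors in the text, easily corrected.

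*Different bands are not a contradiction.* A reader might infer that the subgroups must match the 16–24/25–39 bands used for selection and in Table 1. Nothing in the article requires that. Balancing invitations, adjusting for age and defining exploratory strata are separate uses, and the Discussion's reasoning fits a teens/twenties/thirties split. Merging teenagers with people in their early twenties would blur that contrast. This part stands.

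*The fit figures rest on assumptions.* A reader might also infer that the stratum models mostly or usually cannot be fitted. The documents do not support that. They give no help-seeking proportion, beyond the general remark that formal help-seeking is low among young people, and no class frequencies. In the older bands most fits exist at 20% and 30%. In the youngest band, with sparse classes removed and 50% help-seeking, separation is only 18–20% (n=61) or 4–7% (n=81). A design of 10 binary factors at 35% and 11 continuous ones gives 93/56/19% at n=61 and 63/10/2% at n=81. That design is kinder than Table 1, which has a five-class cancer type and three-class employment and region, but it shows how far the answer depends on the class mix. Separation confined to one rare class may also spoil only that coefficient.

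*Only the starting model was simulated.* The univariable odds ratios do not need it, and elimination may end in a model that can be fitted. So it is not shown that the final reported odds ratios would be infinite. The analysis is also declared exploratory, which limits the consequence.

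**Conclusion.** Two findings hold on the text alone: the first band is labelled from 15 although eligibility starts at 16, and the Table 1 age factor cannot enter the models for the first and third bands, so at most 17 of the 18 factors are estimable there.

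The third is conditional. If the youngest band holds about 61–81 respondents and help-seeking is 10–30%, there are about 6–24 events for about 22 coefficients. The full starting model would have no finite estimate in roughly 20–99% of samples, depending on band size, event rate and sparsity of classes, and where it can be fitted, 0.3–1.1 events per coefficient is too few for a stable result. For 20–29 and 30–39 the problem is serious mainly at about 10% help-seeking.

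The cause is the combination of stratifying and restarting from all 18 factors. The choice of three bands is not itself an error. For an exploratory analysis the consequence is moderate, but the correction is cheap and worth making.

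**What to change.** In the Statistical analysis section:
1. Relabel the first band 16–19.
2. State that the 16–24/25–39 age factor is left out of the band models where it is constant.
3. Replace the fresh elimination from all 18 factors with estimation, in each band, of only the factors retained in the main model (taken here as about 6 parameters), using Firth's penalised likelihood where events are sparse.
4. Report frequencies only for a band with too few events.

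Moving to 16–24/25–39 is optional. It would give a larger youngest group, but at the price of the contrast between adolescents, twenties and thirties, and on its own it does not solve the problem at low help-seeking.

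The cost is a sentence or two of text. The small downside is that predictors specific to one age band, and not retained in the main model, are no longer searched for in the multivariable band models. The univariable odds ratios remain available for them.
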